## ABBREVIATIONS

|           |                                                         |
|-----------|---------------------------------------------------------|
| ACT       | Artemisinin based combination treatment                 |
| AE        | Adverse event                                           |
| AL        | Artemether lumefantrine                                 |
| AS        | Artesunate                                              |
| CarboxyPQ | Carboxyprimaquine                                       |
| CRFs      | Case Report Forms                                       |
| CTCAE     | Common Terminology Criteria for Adverse Events          |
| DHAPP     | Dihydroartemisinin piperazine                           |
| DMEC      | Drug Monitoring and Ethics Committee                    |
| DRC       | Democratic Republic of Congo                            |
| EC        | Ethics Committee                                        |
| G6PD      | Glucose-6-Phosphate Dehydrogenase                       |
| GCP       | Good Clinical Practice                                  |
| HNV       | Human Normal Volunteer                                  |
| IBD       | Inherited blood disorder                                |
| ICH       | International Conference on Harmonization               |
| KEMRI     | Kenya Medical Research Institute                        |
| KIMORU    | Kinshasa Mahidol Oxford Tropical Medicine Research unit |
| KM        | Kaplan Meier                                            |
| MDA       | Mass Drug Administration                                |
| MoH       | Ministry of Health                                      |
| MORU      | Mahidol Oxford Tropical Medicine Research unit          |
| MRC UK    | Medical Research Council, United Kingdom                |
| MTA       | Material Transfer Agreement                             |
| PCR       | Polymerase Chain Reaction                               |
| PD        | Pharmacodynamic                                         |
| PI        | Principal investigator                                  |
| PK        | Pharmacokinetic                                         |
| PQ        | Primaquine                                              |
| SAE       | Serious Adverse Event                                   |
| SPC       | Summary of Product Characteristics                      |
| WT        | Wellcome Trust                                          |

### Amendment history

| Amendment No.                                                                                                                                                                                                                                                                                                                                         | Protocol Version No. | Date issued | Author(s) of changes                                                        |
|-------------------------------------------------------------------------------------------------------------------------------------------------------------------------------------------------------------------------------------------------------------------------------------------------------------------------------------------------------|----------------------|-------------|-----------------------------------------------------------------------------|
| 1                                                                                                                                                                                                                                                                                                                                                     | 2.0                  | 01 Sep 2018 | [name]
[name]
[name]
[name] |
| Details of Changes made                                                                                                                                                                                                                                                                                                                        |                      |             |                                                                             |
| 
 
Added [name] as PK coordinator (List of investigators)
 
Replaced ‘parent’ with ‘caregiver’ throughout the document
 
Added option of testing for G6PD status using FST (Sections 3.2 and 3.9)
 
Revised inclusion age from 11 to <12 years for clarity (Section 3.5)
 
 |                      |             |                                                                             |

- Revised severe anaemia to Hb<6g/dL in the exclusion criteria (Section 3.6)
- Revised the admission to hospital to allow more flexibility during the first few days in the hospital.( Section 3.10.6)
- Hb data will be sent weekly to DMEC (Section 3.10.6)
- Revised the blood volume for clarity (Section 3.10.8)
- Revised consent withdrawal for clarity (Section 4.2)
- Revised window period for follow-up visit (Section 4.3)
- DHAPP dosing is revised to match with the DHAPP formulations available onsite (Section 5.2)
- Revised 30 mins to 60 mins for observation after drug administration (Section 5.4)
- Gametocyte quantification by qPCR technique is revised (Section 7.1.3)
- Reduced number of patients for PK sampling from 400 to 300 per site (Section 7.2)
- Added the USA where samples will be sent to (Section 7.3)
- Revised the adverse event recording to record all grades (Section 8.3)
- Revised indication for transfusion, i.e. Hb< 4-.6 is now 5 g/dL and removed hyperparasitaemia (Section 10.2)

## 1 BACKGROUND & RATIONALE

In September 2012, the World Health Organization (WHO) Evidence Review Group (ERG) recommended adding single low-dose primaquine (SLDPQ, 0.25 mg base/kg body weight, 15 mg for adults) to artemisinin combination therapies (ACTs), without testing for glucose-6-phosphate dehydrogenase deficiency (G6PDd), in nonpregnant, *P. falciparum* infected patients aged  $\geq 1$  year (later amended to  $\geq 6$  months) to block *Plasmodium falciparum* gametocyte transmission from humans to mosquitoes.

This recommendation was aimed primarily at countries of the Greater Mekong Subregion (GMS) where artemisinin-resistant *P. falciparum* (ARPf) is well established, continues to emerge, and has contributed to the failure of dihydroartemisinin-piperaquine (DHAPP), the first-line ACT in Cambodia.

ARPf is now at the threshold of the Indian subcontinent and the great fear is that it will eventually reach Africa where it may lead to substantial reversals in malaria control achieved by the widespread use of ACTs.

The 2012 recommendation was pragmatic, taking into account the lack of detailed, carefully conducted dose-optimisation studies of PQ, the reluctance to use PQ in the GMS because of the fear of PQ-induced acute haemolytic anaemia (AHA) in G6PDd patients, the logistical impossibility of testing widely for G6PDd, and the urgency to eliminate ARPf in the GMS before it spreads to Africa. The ERG also called for more research on SLDPQ.

### *Single low-dose primaquine (SLDPQ) in Africa*

There have been few studies of SLDPQ in Africa. Efficacy studies assessing PQ have been in G6PD normal patients and have used either DHAPP or artemether lumefantrine (AL). One dose ranging study of PQ in G6PD normal patients suggested that the minimum dose of PQ to produce a maximum reduction in mosquito infectivity was probably  $\sim 0.125$  mg/kg whereas a Chinese study suggested a PQ dose between 0.0625 and 0.125 mg/kg of PQ.

Studies assessing the safety of SLDPQ, have been in G6PDd and normal individuals with asymptomatic falciparum malaria; entry to such studies has required a high initial Hb concentration e.g.  $\geq 11$  g/dL (SAFEPRIM - NCT02174900, SAFEPRIM-II - NCT02654730). Data from the latter study were presented in 2015 but have not yet been published. They show that there were mild falls in Hb in the G6PDd individuals that was similar to G6PD normal individuals who received 0.2 or 0.4 mg/kg of PQ, but little change in the G6PDd group that received AL alone.

However, when 0.75 mg/kg of PQ was given to African children  $< 12$  years old with one dose of sulphadoxine-pyrimethamine, those homozygous or hemizygous for G6PDd had greater falls in mean Hb than heterozygous females and those who were G6PD normal. G6PDd patients with greater falls in Hb were also those who received greater mg/kg doses. Indeed, an examination of the PQ dosing regimen used shows that many children received doses in excess of 0.75 mg/kg. No PQ pharmacokinetic work (PK) was done in this study.

There is a broad consensus that dosing regimens should be simple and, in settings where dosing by weight is not possible, to have effective and tolerated drug regimens based on age. Several ACTs have both age and weight band recommendations. No age based dose regimen exists for SLDPQ but one has been proposed for Cambodia ([name], *in press*). An age based regimen of SLDPQ for Africa would be an advance and is proposed in this study.

### *Pharmacology*

There has been very little PQ PK work and most of this work is in adults. Modelled data from one study in healthy G6PD normal children aged 5-12 years from Papua New Guinea (PNG) found PQ PK characteristics equivalent to those in adults. This is a potentially significant finding because a failure to appreciate that children  $< 5$  yrs have higher clearance rates of some antimalarial drugs compared to

adults has resulted in under dosing of sulphadoxine pyrimethamine and DHAPP. There are no PQ PK data in young African children with *P. falciparum* malaria.

PQ has several metabolic pathways and undergoes hepatic oxidative deamination to its principal, inactive metabolite, carboxyPQ (cPQ), chiefly by monoamine oxidase (MAO) A. Cytochrome (CYP) P450 isoenzymes 2D6, 2C19, and 3A4 are quantitatively less important but CYP 2D6 is fundamental to PQ's pharmacodynamic (PD) effects. CYP 2D6 produces oxidative metabolites (OMs) that cause acute haemolytic anaemia (AHA), dose-dependent oxidation of Hb to metHb, and are key to PQ's antirelapse efficacy and, probably, its gametocytocidal effect.

CYP 450 2D6 activity is under polymorphic genetic control resulting in several metabolic patterns: poor (poor efficacy, less dose-related toxicity), intermediate, extensive (normal), and ultrarapid/ultraextensive (potentially enhanced efficacy and dose-related toxicity). The genetic bases for these metabolic phenotypes are complex and their clinical predictive value unclear.

### Summary

Similar to their counterparts in SE Asia, African Ministries of Health (MoH) have been reluctant to adopt SLDPQ because of PQ's toxicity, the lack of a paediatric formulation, the limited number of PQ tablet strengths and the lack of an easy to use dosing regimen.

This study proposal answers the WHO's call for more research on SLDPQ and will fill a number of substantial knowledge gaps in young African children, particularly as we propose using both AL and DHAPP. AL is the first line ACT in Uganda and the DRC whilst DHAPP is a favoured drug for malaria elimination because of its excellent tolerability and long half-life.

Testing DHAPP in this large trial will also allow us to compare the PK of SLDPQ in DHAPP and AL treated children. Other knowledge gaps we will fill include the: (i) tolerability of SLDPQ at the WHO recommended dose in children with high biomass falciparum infections and frequent concomitant anaemia, (ii) factors associated with the development of severe/profound anaemia, and (iii) prevalence rates of CYP 2D6 polymorphisms and their relationships to PQ PK.

## 2 AIMS & OBJECTIVES

The aim of this study is to provide evidence for drug policy on the safety of the WHO recommended SLDPQ regimen when used under close to routine conditions to G6PDd African children with acute uncomplicated *P. falciparum*.

### 2.1 Primary Objective

The primary objective will answer this research question: is a single low but gametocytocidal dose of PQ (0.25 mg/kg) safe and well tolerated when added to AL or DHAPP for treating glucose-6-phosphate dehydrogenase deficient African children with acute uncomplicated *P. falciparum* malaria?

### 2.2 Secondary Objectives

These are to:

- explore risk factors for developing profound or severe anaemia in this trial
- model the determinants of changes in haemoglobin concentrations over time
- characterise G6PD deficiency, other inherited blood disorders (IBDs) and the cytochrome 2D6 polymorphisms
- define the PK characteristics of PQ, cPQ, lumefantrine and piperaquine
- determine changes in gametocyte carriage over time
- measure the parasite clearance over time and the D42 cure rate

- assess the test characteristics of a G6PD Biosensor

### 3 STUDY METHODS

#### 3.1 Study sites

The study will take place in Kinshasa in the Democratic Republic of Congo and in Uganda.

In Kinshasa, the Kinshasa Mahidol Oxford Tropical Medicine Research unit (KIMORU) has a clinical laboratory, a 15 bedded ward, and a full-time, GCP trained, research team of doctors, nurses and laboratory technicians. Malaria transmission is intense and KIMORU sees ~10,000 outpatient malaria cases/year from the Kinshasa conurbation, mostly children under five years of age.

The Mbale Regional Referral Hospital is situated in eastern Uganda in an area of perennial hyperendemic malaria. It serves a wide, predominantly rural, catchment area. Annual admissions to the paediatric ward are ~20,000 and approximately 140 patients per day are seen in outpatients of whom some 110 have malaria ([name], unpublished)

#### 3.2 Study design

This is a randomised, multicentre, parallel-group safety trial of SLDPQ when combined with the first-line antimalarial therapy, AL, or DHAPP for treating acute uncomplicated *P. falciparum* malaria in G6PDd and G6PD normal African children. The trial is double blind with respect to SLDPQ but AL and DHAPP are open.

The trial will be stratified by G6PD status based on the results of a G6PD rapid diagnostic test (RDT)\*:

- a G6PDd group that will be randomised to AL or DHAPP plus SLDPQ or placebo, and
- a G6PD normal group that will be randomised to AL or DHAPP plus SLDPQ or placebo

\* we will use the AccessBio G6PD RDT. If a site also wishes, the fluorescent spot test (FST) can be used. Where there are discrepant FST RDT results, preference will be given to the FST.

#### 3.3 Primary Endpoint

The primary outcome is the proportion of patients who, within the first 21 days, develop either:

- profound anaemia [Hb concentration < 4g/dL] or
- severe anaemia (Hb <5g/dL) with severity features e.g. impaired consciousness or deep breathing.

#### 3.4 Secondary endpoints

The secondary endpoints are to determine/measure/assess:

- Haemoglobin concentrations over time:
  - Fractional change in haemoglobin on Day 7 vs. baseline
  - Proportion of patients with a fractional change  $\geq 25\%$
  - Time to nadir Hb concentration
- Determinants of changes in Hb concentration over time
- G6PD genotype (hemizygous male, homo-, heterozygous female, normal and selected G6PD variants e.g. G6PD A- 202 mutation)
- G6PD enzyme activity

- Genotypes of other inherited blood disorders
- Incidence of adverse events
- Pharmacokinetic characteristics of PQ, carboxyPQ, lumefantrine and piperaquine
- CYP 2D6 genotypes
- Asexual parasitaemia clearance time and half life
- Therapeutic efficacy of AL and DHAPP using the WHO criteria (Appendix 3)
- Gametocytaemia over time
- Proportion of patients with gametocytes over time

### 3.5 Inclusion criteria

- Age  $\geq$  6 months to <12 years
- Presentation with:
  - clinically uncomplicated disease
  - fever ( $\geq 37.5^{\circ}\text{C}$  aural) or history of fever within the previous 72 hours, and
  - a positive malaria slide for *P. falciparum* (mono or mixed infection) of any parasitaemia (Kinshasa only)
- Informed consent provided by patient or relative/legal guardian

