### 3.6 Exclusion Criteria

The patient/subject will not enter the study if ANY of the following apply:

- Malaria danger signs, sign(s) of severe malaria, or decompensated anaemia, including:
  - An inability to take or retain fluids or oral medications
  - Confusion
  - Prostration
  - Convulsions
  - Respiratory distress
  - Passing of red or cola-coloured urine (putative “blackwater fever”)
- Hb <6 g/dL
- A comorbid illness that requires treatment in hospital (physician’s judgement)
- Patients on drugs known to cause haemolysis in G6PDd e.g. dapsone, nalidixic acid
- Known to be allergic to PQ, AL, or DHAPP
- Previous enrolment in the current trial or current enrolment in another trial

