## 5 STUDY DRUGS

### 5.1 Artemether lumefantrine

AL is the recommended first line drug for falciparum malaria in DRC and Uganda.

GMP manufactured AL will be obtained from a reliable manufacturer or official supplier either locally or externally and imported. If imported all necessary documentation will be obtained (e.g. certificate of analysis, etc). AL will be dosed by weight, in accordance with the manufacturer's recommendation. One tablet of dispersible and non-dispersible AL contains 20 mg of artemether and 120 mg of lumefantrine.

AL is dose twice daily. On the first day of treatment the doses are separated by 8 hours but by 12h on the second and third days of treatment. The total course is 6 doses.

| Weight in kg | Number of tablets / dose | Total number of tablets / day | Total number of tablets / course |
|--------------|--------------------------|-------------------------------|----------------------------------|
| 5 - <15      | 1                        | 2                             | 6                                |
| 15 - < 25    | 2                        | 4                             | 12                               |
| 25 - < 35    | 3                        | 6                             | 18                               |
| ≥ 35         | 4                        | 8                             | 24                               |

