### 5.2 Dihydroartemisinin piperazine

DHAPP has been extensively used in Africa and Asia and the Sigma Tau formulation is registered in several African countries and was registered in the European Union in 2011.

GMP produced DHAPP will be obtained from a reliable source and, if imported, all necessary documentation will be obtained. DHAPP will be dosed by weight. The 2015 WHO guidelines now recommend a dose of  $\geq 2.5$  mg/kg/day of DHA in children who weigh  $< 25$  kg (<http://www.who.int/malaria/publications/atoz/9789241549127/en/>).

There are three DHAPP tablet strengths, all in mgs:

- DHA 20 PP 160
- DHA 40 PP 320
- DHA 80 PP 640

The teams will modify the WHO dosing chart according to the tablet strengths they are able to obtain in Kinshasa and Uganda.

Table 1. DHAPP dosing table from the WHO.

| Body weight (kg) | Dihydroartemisinin + piperaquine dose (mg) given daily for 3 days |
|------------------|-------------------------------------------------------------------|
| 5 to < 8         | 20 + 160                                                          |
| 8 to < 11        | 30 + 240                                                          |
| 11 to < 17       | 40 + 320                                                          |
| 17 to < 25       | 60 + 480                                                          |
| 25 to < 36       | 80 + 640                                                          |
| 36 to < 60       | 120 + 960                                                         |
| 60 < 80          | 160 + 1280                                                        |
| >80              | 200 + 1600                                                        |

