### 5.3 Primaquine/placebo

PQ/placebo (2.5, 5, 7.5 mg PQ base) will be manufactured for this trial by Centurion Remedies, PVT Ltd, Gorwa, India. This is a WHO certified manufacturing facility. Bilcare Ltd, Pune, India, will blister pack the PQ/placebo and will manage their export from India to the DRC and Uganda, in accordance with all applicable drug regulations.

Bilcare Ltd has already supplied quality, GMP manufactured PQ/placebo for MORU for another large trial (NCT01814683). The batch of PQ/placebo used for this trial will be quality controlled and a certificate of analysis will be supplied by Bilcare Ltd.

Dosing will be by age. The target dose of PQ is 0.25 mg/kg with a therapeutic dosing range of 0.15 - 0.4 mg/kg given once with the first dose of AL or DHAPP. Children will receive doses ranging from 0.1 - 0.46 mg/kg. A detailed breakdown of the mg/kg dose that a child will receive is shown in Table 2.

For young children who cannot swallow, the PQ/placebo tablet will be dissolved in 5 mL of sugar water (or similar solution depending on local practice) and the dose administered. The 2.5 mg PQ/placebo tablet will be used for children aged 6-11m but they will be given 2.5 mL of suspension and so will receive 1.25 mg of PQ/placebo. Guidelines on the practicalities of drug administration will be written.

Table 2. Dosing table by age of PQ showing the mg/kg dose received.

| Age   | Primaquine dose in mg base | minimum | 1 st quartile | median | 3 rd quartile | Maximum |
|-------|----------------------------|---------|--------------------------|--------|--------------------------|---------|
| 6-11m | 1.25                       | 0.1     | 0.15                     | 0.16   | 0.18                     | 0.3     |
| 1y    | 2.5                        | 0.16    | 0.25                     | 0.27   | 0.3                      | 0.46    |
| 2y    | 2.5                        | 0.14    | 0.2                      | 0.22   | 0.25                     | 0.37    |
| 3y    | 2.5                        | 0.12    | 0.17                     | 0.19   | 0.21                     | 0.32    |
| 4y    | 2.5                        | 0.11    | 0.16                     | 0.17   | 0.19                     | 0.29    |
| 5y    | 2.5                        | 0.1     | 0.15                     | 0.16   | 0.18                     | 0.25    |

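### Eligibility is by age with no weight limit, but both ACT tables start at 5 kg, and the primaquine table implies an eligible infant of about 4.2 kg

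*Protocol*

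**What the plan says.** - **Eligibility.** Section 3.5 sets the age range at "6 months to <12 years" and gives no weight. Section 3.6 opens with "The patient/subject will not enter the study if ANY of the following apply". Its list covers severity signs, haemoglobin, comorbid illness, haemolytic drugs, allergy and other enrolment, but not body weight.
- **ACT dosing.** Section 5.1 states "AL will be dosed by weight, in accordance with the manufacturer's recommendation", and section 5.2 states "DHAPP will be dosed by weight". The lowest band is 5 to under 15 kg for AL and 5 to under 8 kg for DHAPP. Sites may adapt the DHAPP chart, but only to the tablet strengths they can obtain.
- **Primaquine dosing.** Section 5.3 doses by age. Infants aged 6-11 months are given half of a dissolved 2.5 mg tablet and "so will receive 1.25 mg of PQ/placebo". The section introduces its table with "A detailed breakdown of the mg/kg dose that a child will receive is shown in Table 2" and summarises it with "Children will receive doses ranging from 0.1 - 0.46 mg/kg".
- **When weight is taken.** Section 7.1.1 has weight recorded at screening, to the nearest kilogram. The test lists in 3.7.1 and 3.7.2 do not mention it. Appendix 1 places it in the block for enrolled patients, after the row that assigns the study number.
- **Recruitment.** Section 3.10.3 aims for at least 80 children aged 6-11 months and may suspend other age groups to balance recruitment.

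**The concern.** One study drug is dosed by age and the other two by weight, while entry depends on age alone. An infant who meets every criterion could weigh less than the first row of both ACT tables. The protocol's own primaquine table suggests that such infants were in view when the age bands were set.

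If such a child is randomised, the allocation names an ACT for which the protocol gives no dose. The site would have to find a dose outside the protocol or leave the ACT ungiven. In the second case the child falls outside the section 11.2 analysis population, which requires receipt of both the ACT and PQ/placebo. That would be an exclusion after randomisation.

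**Working it through.** **Inputs.** From section 5.3, Table 2: fixed PQ dose and mg/kg by age. From 5.1 and 5.2: lower limit of 5 kg in both ACT tables. From 7.1.1: weight rounded to the nearest kilogram.

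**1. Reproduce the plan's own figure.** Over all age rows of Table 2, the smallest minimum is 0.1 mg/kg (6-11 months and 5 years) and the largest maximum is 0.46 mg/kg (1 year). This matches the range of 0.1 to 0.46 stated in 5.3, so the table is being read correctly.

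**2. Implied weights at 6-11 months.** Weight = dose in mg / dose in mg/kg, with a dose of 1.25 mg:

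| Table 2 column | mg/kg | Implied weight (kg) |
|---|---|---|
| Minimum | 0.1 | 12.50 |
| First quartile | 0.15 | 8.33 |
| Median | 0.16 | 7.81 |
| Third quartile | 0.18 | 6.94 |
| Maximum | 0.3 | 4.17 |

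The lightest implied child is 5 - 4.17 = 0.83 kg below the first band of both ACT tables. At exactly 5 kg the dose would be 1.25/5 = 0.25 mg/kg, so any value above 0.25 in this row means a weight under 5 kg.

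**3. Rounding of the table entry.** If 0.3 stands for 0.30 to two decimals, the implied weight lies between 1.25/0.305 = 4.10 kg and 1.25/0.295 = 4.24 kg. If it was rounded to one decimal, the range is 1.25/0.35 = 3.57 kg to 1.25/0.25 = 5.0 kg. The row also contains 0.15, 0.16 and 0.18, so two decimals is the natural reading.

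**4. Rounding of the recorded weight.** A child of 4.5 to 4.99 kg is recorded as 5 kg and falls in the first band of both tables. A child of 4.17 kg is recorded as 4 kg and does not. The uncovered range is therefore below about 4.5 kg actual weight: narrower than a 5 kg floor suggests, but not empty.

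**5. Other ages.** The next lightest implied child is at 1 year: 2.5/0.46 = 5.43 kg, which both tables cover. At the top, 11 years gives 7.5/0.16 = 46.9 kg, also covered by both. The mismatch is confined to 6-11 months.

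**6. Order of events.** Under 3.8 the study number follows signed consent, and under 3.10 the allocation envelope is opened after the number is given. Section 7.1.1 puts weighing before this; Appendix 1 lists it after the number. Neither place, nor any other, tells staff to compare weight with the ACT tables.

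**The case against.** The strongest reply is that this is a gap and not a flat contradiction. No section promises an ACT row for every eligible child, and the weight under 5 kg is back-calculated from one extreme cell of a table whose weight source section 5.3 does not state. That is fair. But 5.3 presents the table as what children in this trial will receive, and the mismatch between age-only entry and two weight tables with a common 5 kg floor exists without that cell.

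A second reply is that an infant this light might be excluded on the physician's judgement of comorbid illness. That may happen, but it is not a weight rule.

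A third is that details are left to other documents: the manufacturer's recommendation for AL, the site adaptation of the DHAPP chart, and guidelines on drug management and administration still to be written. The protocol reproduces the AL recommendation only from 5 kg, the DHAPP adaptation concerns tablet strengths, and neither guideline is said to cover this case. They are not at hand, so it cannot be said that they omit it.

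A reader might infer that the child would be numbered and allocated before anyone knew the weight. The documents do not support that: 7.1.1 has weight taken at screening. The lists in 3.7.1 and 3.7.2 are mainly lists of blood tests, so their silence counts for little alone. What is missing is an instruction to act on the weight, together with agreement between 7.1.1 and Appendix 1 on its timing.

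A reader might also infer that each such child is a safety event, or that a dose chosen outside the tables is automatically a violation. Section 4.5 lists giving a wrong dose as a violation but does not address a dose for which no row exists. Nor do the documents show that infants under 5 kg are especially anaemic; the background section speaks of frequent anaemia in the trial's children generally.

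**Conclusion.** The point holds at low severity. As written, the eligibility rules admit a child aged 6-11 months weighing less than about 4.5 kg, for whom neither ACT table gives a dose. Table 2 implies that a child of about 4.2 kg (4.10 to 4.24 kg) was anticipated. This rests on two assumptions: that 0.3 is a two-decimal entry, and that Table 2 describes the children the trial will enrol, as 5.3 says. If 0.3 were a one-decimal entry, the table alone would no longer prove a weight below 4.5 kg, but the eligibility and dosing sections would still not match.

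The number affected is small and cannot be derived. The third-quartile dose implies that three quarters of the group weigh about 6.9 kg or more, so the uncovered children are somewhere in the lightest quarter. The planned minimum for the group is 80 of 1600 children, or 5% of the trial. Both ACT tables share the same floor, so the gap does not differ by ACT or between PQ and placebo, and no effect on the non-inferiority conclusion is shown. The consequence is limited to an undefined ACT dose or a possible post-randomisation exclusion.

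**What to change.** 1. Reconcile 3.5 and 3.6 with 5.1, 5.2 and Table 2 so that every eligible child falls within the range both ACT tables cover. Whether this is done through eligibility or through the tables is for the sponsor to decide.
2. Align Appendix 1 with 7.1.1 on when weight is taken.
3. Add a step that checks the recorded weight against the reconciled range before the study number is issued.

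The cost is a few lines of wording and one entry on the screening form, since 7.1.1 already calls for weight at screening. The downside is that a few infants may be screened out if the sponsor chooses the eligibility route.
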